### Recruitment {15}

The recruitment will take place in autumn 2022. Schools are the most appropriate setting for universal prevention for the following reasons: (1) An adolescent’s life is mostly played out at school, (2) compulsory school attendance provides the opportunity to reach a large number of adolescents, and (3) there is evidence that students are more likely to accept such programmes within school than during their free time. The School Boards will help us to get in touch with eligible schools. *LessStress* targets classes from the 6th to 12th grade at public and private schools. Any school principal or council expressing an interest can officially register for potential participation via mail. In a next step, further information material regarding the study will be sent out if required. If schools agree to participate, a letter of consent has to be signed, stating how many grades and classes will participate in *LessStress*.

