One extremely important conclusion that can be drawn from the ongoing pandemic situation is that children and young people are suffering [6–8] due, among other factors, to adverse home conditions, family stress, or mental illness. Therefore, it is essential to provide rapid assistance and to develop and evaluate effective, efficient prevention programmes that are easy to access and implement [6]. As child and adolescent mental health is hugely multifaceted [7], we limit ourselves here to one risk factor of which we are all aware, and with which students have struggled a great deal over the last 2 years: stress [1, 2]. A very broad definition of stress goes back to Hans Selye, a twentieth-century physician, biochemist, and hormone researcher, who said “Stress is the nonspecific response of the body to any demand” [9]. There are many different definitions of stress depending on the context. In the behavioural sciences, stress describes the perception of a threat, which is reacted to with anxiety, emotional tension, and discomfort. Neuroendocrinological stress can be described as a reaction of the body, more precisely the sympathetic nervous system, to release ACTH and adrenal glucocorticoids in response to a stimulus [10]. In the psychological context, it is assumed that the induction of negative affective states (e.g. feelings of anxiety and depression) influences the pathogenesis of physical illnesses [11]. Chronic stress is likely to result in long-term or lasting changes in emotional, physiological, and behavioural responses, which in turn affect susceptibility to and progression of disease, including stressful events such as trauma [12]. The endocrine response triggered by stress is composed of two endocrine response systems that are particularly responsive to psychological stress: the hypothalamic-pituitary-adrenal (HPA) axis and the sympathetic-adrenal medulla (SAM) system [13, 14]. Cortisol as the primary effector regulates a wide range of physiological processes. The repeated and prolonged activation of the HPA and SAM systems can severely impair physiology and is therefore at increased risk for physical and psychiatric disorders [11]. Symptoms associated with stress include loss of appetite, headache, stomach pain, difficulty concentrating, sleep disorders [15], and a decrease in QoL [16]. Stress is perceived differently from person to person, has a cumulative effect, and is seen as one of the strongest predictors of mental illness [15, 17]. A survey of around 230,000 6–18-year-olds conducted by the Kaufmännische Krankenkasse in 2017 [18] revealed a significant increase in mental disorders among children and adolescents with stress being identified as the major issue. Another prospective cohort study reported depression or neurotic and somatoform disorders to be the main disorders comorbid to stress [19]. This finding is supported by a body of evidence conducted in other studies [20–22]. The increased stress in young people pertains not only to school and academic achievement, but also to further factors such as stress with parents (regarding both school and home life), overstimulation by media, bullying in social networks, or general fears, which all contribute to a higher stress perception. School and school-related stress is certainly a major concern, even in elementary school: Young children are vulnerable to stress and show stress symptoms, and it has been identified that girls are more susceptible to stress and are coping differently compared to boys [20, 23]. Stress levels among children and adolescents appear to be higher in more academic school types than in vocational schools [24], and rise during adolescence [25]. With respect to school, and specifically stress caused in school, it is necessary to address and prevent anxiety (separation anxiety, fear of school, social anxiety, and test anxiety) together with the students themselves [26]. Crucially, moreover, stress leads to neurocognitive alterations [27].

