### Who will take informed consent? {26a}

For the trial, the informed consent of the respective schools’ head teachers is required, as well as the informed consent of a legal guardian and of the students. If schools express an interest in participating, a meeting will be organised in order to provide detailed information about the study. In the case of participation, the legal guardians of students in the participating grades/classes will be given detailed written information sheets and will be able to watch an online presentation, in which the study is orally explained. The students will receive posters with information. If students wish to participate, they will provide their written consent by clicking on “Yes, I do want to participate in the study” on the first page of the online survey.

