### Participant timeline {13}

All participants will be assessed using the full battery of instruments as displayed in Table 1. The data assessment will take place 14–30 days after randomisation. For the intervention group (IG), the universal prevention programme *LessStress* will be administered by school staff within the 21 days after baseline. Post-assessment is due within a week after participating the lesson of *LessStress*. Follow-up interviews, using the full battery of questionnaires, will be conducted at 3 months (T2, 104–120 days) and 6 months (T3, 194–210 days) after randomisation. A 14-day window (± 7 days) will be permitted within which to schedule the time points for T2 and 3. For a graphic overview of the study, please see the flowchart in Fig. 2.

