## Assignment of interventions: allocation

### Sequence generation {16a}

Participating schools will be randomly assigned to one of the two groups using Microsoft Excel. The randomisation will be carried out on the school level following a 1:1 allocation ratio. This enables interference between the IG and WL to be avoided.

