### Concealment mechanism {16b}

The schools will be immediately informed about the allocation via mail. For randomisation, we will use Microsoft Excel. To proceed with organising the appointments and the intervention, schools have to know to which group they have been allocated. The allocation will be executed in the presence of a third independent employee of the clinic (SM).

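### The school's letter states how many grades and classes will take part, but nothing fixes which ones before the draw, so they can be chosen with the arm known

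*Protocol article*

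**What the plan says.** The order of events has to be pieced together from several sections of the protocol article.

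- **Recruitment {15}:** once a school agrees to join, "a letter of consent has to be signed, stating how many grades and classes will participate". What the letter is said to record is a count.
- **Sequence generation {16a}:** "Participating schools will be randomly assigned to one of the two groups using Microsoft Excel", and "The randomisation will be carried out on the school level following a 1:1 allocation ratio".
- **Concealment mechanism {16b}:** "The schools will be immediately informed about the allocation via mail".
- **Participant timeline {13}:** for baseline, "The data assessment will take place 14–30 days after randomisation".
- **Who will take informed consent? {26a}:** when a school takes part, "the legal guardians of students in the participating grades/classes will be given detailed written information sheets". Students give their own consent "on the first page of the online survey".
- **Implementation {16c}:** the authors expect no bias from sequence generation or poor concealment, on the ground that the study involves no patients.

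No section says that the classes are named or locked before the draw, or who selects them. Study setting {9} adds that the number of schools or classes cannot yet be foreseen.

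**The concern.** In a cluster trial, randomising schools protects the comparison only if the students who will be studied in each school are settled before the arm is known. If a school has fixed a number but not a list, whoever fills that number can do so knowing the arm.

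The arms face different practical demands. An intervention school must find staff to train and deliver the lesson within 21 days of baseline (Participant timeline {13}). A waiting-list school at first only has to run surveys. The classes entered may therefore differ systematically by arm, without any bad faith.

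This is separate from individual uptake. Complete consent within the chosen classes would not repair a biased choice of classes.

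The planned analysis compares arms on the difference in change. If classes in one arm were entered because they were under particular stress at the time, part of that excess would fade by follow-up and look like a programme effect. A random intercept for class or school models correlation and does not remove a systematic difference between arms. Adjusting for baseline would help only in part.

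**Working it through.** **Step 1: the order of events.** The article states no figure on this point, so the first check is to set the sections side by side.

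1. The school agrees and signs a letter giving the number of grades and classes (Recruitment {15}).
2. Schools that are already participating are randomised 1:1 (Sequence generation {16a}). That the letter comes before the draw follows from this wording; it is not dated.
3. Schools learn their arm at once (Concealment mechanism {16b}).
4. Baseline takes place 14 to 30 days later (Participant timeline {13}).
5. Student consent is given on opening the survey (consent section {26a}), so after step 3.

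Between steps 3 and 4 there are at least 14 days in which the arm is known and no stated rule fixes the classes. The reason given under Implementation {16c}, that no patients are involved, has no bearing on this interval. The reason given for randomising by school is to avoid interference between arms, which concerns contamination and not selection.

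**Step 2: how large a distortion could be (illustration only).**

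Inputs:
- ICC = 0.05, from Sample size {14}. There it belongs to a cluster of about 80 students, a whole grade; here it is borrowed as a between-class value.
- Selection intensity i = 0.4 to 0.8 class-SD, in one arm only (assumed).
- Share of the excess that is temporary, t = 0.3 to 0.6 (assumed).
- Planned effect d = 0.2 (Sample size {14}).

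Formulas:
- Class-SD in units of the total SD = √ICC = √0.05 = 0.224.
- Baseline gap = i × √ICC: 0.4 × 0.224 = 0.089 SD, up to 0.8 × 0.224 = 0.179 SD.
- Spurious difference in change = gap × t: 0.089 × 0.3 = 0.027 SD, up to 0.179 × 0.6 = 0.107 SD.
- As a share of d: 0.027 / 0.2 = 13%, up to 0.107 / 0.2 = 54%.

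Sensitivity to the ICC, over an assumed range of 0.03 to 0.10:
- Low end: 0.4 × √0.03 × 0.3 = 0.021 SD.
- High end: 0.8 × √0.10 × 0.6 = 0.152 SD.

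**Step 3: what such a shift does to the test.** Take the protocol's base N of 306 (153 per arm) at face value as the effective size, and an outcome SD of 1. The standard error is √(2/153) = 0.114. With no true effect, the chance of a significant result in the direction of the shift is Φ(shift/0.114 − 1.96):
- 0.05 SD: about 6%
- 0.10 SD: about 14%

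The nominal value in that direction is 2.5%.

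**The case against.** The strongest reply is that this builds on silence. The article condenses a fuller protocol, the letter form and both figures are not shown, and the form may well list the classes. The consent section also speaks of the participating grades and classes as if they were already defined. This much stands: a reader might infer that a count is all a school ever commits to, or that head teachers hand-pick classes after allocation, and the article supports neither. It does not reproduce the letter, and it does not say who chooses or when. What remains is that the one sentence describing the letter mentions only a number, and that the article goes on to dismiss concealment bias for a reason that does not address the choice of classes.

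The incentives are also less one-sided than they first look. Waiting-list schools are promised the programme directly after the 6-month follow-up (Explanation for the choice of comparators {6b}), so they too have reason to enter classes in need. An intervention school that picks its most willing teachers need not be picking its most stressed students. The direction of any bias is therefore unknown, and similar selection in both arms would largely cancel.

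Sample size {14} plans on whole grades. If whole grades take part, there is little or no choice of class within a grade, but the choice of grade stays open across grades 6 to 12.

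A reader might go on to argue that, since the Background says stress levels are higher in some school types "and rise during adolescence", a difference in grade mix adds further bias. With an assumed trend of 0.03 to 0.08 SD per grade, two grades' difference gives 0.06 to 0.16 SD in level. But a constant difference in level cancels in a comparison of change, and the article does not say that six-month change differs by grade. That figure should not be counted.

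**Conclusion.** The point holds as a design weakness that is cheap to close. As the article is written, grades or classes can be chosen with the arm known, and the assurance under Implementation {16c} does not reach this. It is a route for selection, not evidence that selection will occur.

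Under the stated assumptions the distortion would be about 0.03 to 0.11 SD, or 13 to 54% of the planned effect. That range rests on one-sided selection, an assumed intensity and temporary share, and an ICC borrowed from a grade-sized cluster. It shows that the problem could matter next to an effect of 0.2; it does not estimate a bias. That the letter precedes the draw is itself an inference, though the natural one. The reason to act is that analysis cannot fully undo selection after allocation, while preventing it costs almost nothing.

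**What to change.** Change Recruitment {15} so that the signed letter names the participating grades and classes (for example 7a, 7b, 7c) as well as giving their number. Randomise a school only once that list is filed. Allow no class or grade to be added or swapped after the draw. A listed class that later does not take part stays on the list and is reported as lost, by arm.

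The statement under Implementation {16c} should then refer to this safeguard and not to the absence of patients. If the existing form already names the classes before the draw, correcting the sentence in Recruitment {15} is enough.

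Cost: one line in a form already in use. The downside is that schools must decide on their classes slightly earlier.

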## Assignment of interventions: allocation

### Sequence generation {16a}

Participating schools will be randomly assigned to one of the two groups using Microsoft Excel. The randomisation will be carried out on the school level following a 1:1 allocation ratio. This enables interference between the IG and WL to be avoided.

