### Sample size {14}

To analyse cluster-randomised trials, specific constraints must be followed, as individuals within a cluster are assumed to be more similar compared to individuals from different clusters. In order to detect significant effects, the sample size of the trial must be adjusted. This so-called clustering effect (1 + (*m*-1)×*p* [*m* = average number of subjects per cluster; *p* = intraclass correlation coefficient (ICC)]) resulted in an estimated *N* = 1795. For *m*, we assumed an average of 80 within an entire grade as the average class size in Germany varies nationwide (21.2–30.4 students per class), and the ICC was estimated quite conservatively at approximately 0.05 [70] on the basis of the primary outcome. Hence, a clustering effect of 4.95 was determined. Assuming a small effect size (Cohens *d* = 0.2) in universal prevention based on previous studies [71], with a significance level alpha = 0.05 and a power = 0.9, g*power suggests a total of *N* = 306 [72]. Considering the clustering effect, we have to multiply this by 4.95, reaching an overall *N* = 1515. Assuming a dropout rate of 25% due to moving out of the area, sickness, or other reasons, we must add another 379, leading to the final *N* = 1894.

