## Discussion

According to the latest figures, over 20 million people in Germany are affected by mental illness (prevalence of 27.8%), including 2.7 million children and adolescents [92]. The goal of universal prevention is to increase competencies within a large population without prior selection. We want to contribute to this through the prevention programme *LessStress*. The advantages of *LessStress* lie in its short implementation time, the integration into normal school lessons, and the easy training of already existing school staff. If effects can be proven, a step would be taken towards keeping children and adolescents healthy in the school setting. If *LessStress* does not prove to be effective, it is important to find out what we can improve to bring scientifically evaluated and effective prevention programmes into schools. At the same time, some of the benefits of *LessStress* should also be seen as limitations. In particular, the short implementation time and the implementation by teachers may influence our outcomes. Moreover, the different schools with different requirements for the students could have a negative impact on this study. However, with our adjusted case number estimation, even small effects will be visible, insofar as they exist.

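### Schools are allocated 1:1 in Excel with no balancing on school type, although few clusters are implied and the protocol links school type to stress; stratified or constrained allocation would be a cheap gain in precision and credibility

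*Protocol article*

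**What the plan says.** Allocation is described in three places: Trial design (Randomisation), Sequence generation {16a} and Concealment mechanism {16b}. All three say Excel is used. Randomisation is by school, 1:1, performed by or in the presence of a clinic employee outside the project. The core statement is "Participating schools will be randomly assigned to one of the two groups using Microsoft Excel". No balancing factor or restriction is named. Implementation {16c} expects no bias from the method of sequence generation, on the ground that no patients are involved.

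Elsewhere the protocol treats schools as unlike one another:

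- Background: "Stress levels among children and adolescents appear to be higher in more academic school types than in vocational schools".
- Statistical methods {20a}: school type is listed as one of the levels at which the data are clustered.
- Additional analyses {20b}: comparisons by school type are planned.
- Discussion: "the different schools with different requirements for the students could have a negative impact on this study".
- Study setting {9} and Recruitment {15}: schools come from three federal states, public and private, grades 6 to 12. The number of schools is said to be unpredictable.

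For cluster size and similarity, Sample size {14} says "we assumed an average of 80 within an entire grade" and "the ICC was estimated quite conservatively at approximately 0.05".

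**The concern.** With a few dozen clusters or fewer, simple randomisation does not reliably balance a school characteristic that is related to the outcome. The protocol names such a characteristic, and it is known when a school registers. Leaving it to chance means that between-school variance which could be removed stays in the comparison. A visibly uneven mix of school types would also make a small effect harder to believe in either direction. Implementation {16c} does not answer this: the absence of patients has no bearing on chance imbalance among few clusters.

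**Working it through.** **1. The plan's own figures.** Design effect: 1 + (80 − 1) × 0.05 = 4.95, as stated ("Hence, a clustering effect of 4.95 was determined"). Then 306 × 4.95 = 1514.7, or 1515, and 1515 × 1.25 = 1893.75, or 1894, as stated ("we must add another 379, leading to the final *N* = 1894"). These steps reproduce. The starting value of 306 is a separate matter; the check below uses only the planned total, the cluster size and the ICC.

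**2. Implied number of schools.** 1894 / 80 = 23.7, about 24, or k ≈ 11.84 per arm. This is inferred, since the protocol fixes no number. Because 80 is one grade and Recruitment {15} lets a school enter several, the count could be lower. Two grades per school would give 1894 / 160 = 11.8.

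**3. Chance difference between arms in PSS-10 level** (outcome-SD units, normal approximation).

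- School component: √(2 × ICC / k) = √(2 × 0.05 / 11.84) = 0.092.
- Total: √(2 × [ICC + (1 − ICC)/m] / k) = √(2 × [0.05 + 0.95/80] / 11.84) = 0.102.

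| Schools (assumed) | SD, school / total | P(difference > 0.1 in size) | P(difference > 0.2 in size) |
|---|---|---|---|
| about 24, m = 80 | 0.092 / 0.102 | 28% / 33% | 3% / 5% |
| about 12, m = 160, ICC kept at 0.05 | 0.130 / 0.137 | 44% / 47% | 12% / 15% |

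**4. School type alone.** Assume 24 schools, 12 of them academic, and a forced 12:12 split between arms. The number of academic schools in one arm is hypergeometric, and P(8:4 or worse, either way) = 0.220. An 8:4 split makes the arms differ by (8 − 4)/12 = 1/3 in the share of academic schools. If types differ by 0.2–0.3 SD in stress level (assumption; the protocol gives no figure), the shift is 0.067–0.10 SD.

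The chance that school type alone produces a shift of 0.2 or more is practically nil at a 0.2 SD type difference and 0.3% at 0.3 SD. At the ceiling, type explains the whole ICC: δ²/4 = 0.05, so δ = 0.447. The chance is then 3.9%.

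**5. What balancing could gain.** With 12 schools per arm and adjustment for type, SE = √(2 × [0.05 × (1 − s) + 0.95/80] / 12), where s is the share of between-school variance that type explains (assumed). For s = 0, 0.25 and 0.50 this gives 0.102, 0.091 and 0.078.

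**The case against.** A reader might infer that chance imbalance could rival the target effect, or that it adds directly to the estimated treatment difference. The documents do not support either reading.

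- Statistical methods {20a} compares the arms on change, so a stable difference in stress level between school types largely cancels. The Background evidence concerns levels, and nothing in the protocol says that types differ in their six-month change. This objection stands in part. The Outcomes section words the primary outcome as group differences at 3 and 6 months, and change does not remove different trajectories over the school year, if there are any.
- With about 24 schools, a difference as large as 0.2 is a tail event.
- A reader might also cite the 15% chance of a 16:8 or worse split of schools, with (1/8 + 1/16)/(1/12 + 1/12) = 1.125 times the variance. That holds only if each of 24 schools is drawn independently. The protocol states a 1:1 ratio and does not describe such draws. Even then the standard error rises by only about 6%.
- The Discussion remark about different schools does not mention allocation or imbalance, so it is weak support.
- Unrestricted randomisation is valid, and a cluster-aware analysis carries chance imbalance in its standard error. That is correct in principle. However, {20a} uses multilevel models only if the ICC exceeds 0.1, and the planning value is 0.05. If the mixed ANOVA then ignores schools, its standard error on outcome levels would be too small by about √4.95 = 2.2, and chance imbalance could be read as effect. The protocol does not say whether that ANOVA would account for schools.

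The point is also not mere silence in a condensed article. The sequence must be settled before the first school is allocated, and {16a} is the item that describes it.

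**Conclusion.** The point holds as a cheap improvement, not as an error. No balancing is described, few clusters are implied, and the protocol itself relates school type to stress. With about 24 schools and an ICC of 0.05, the chance difference in stress level has an SD of about 0.10, half the target, and passes the full target in about 3–5% of allocations. Fewer schools would make this worse. The size rests on the inferred school count and the planning ICC. The figures for school type alone rest also on an assumed half of schools being academic and an assumed difference of 0.2–0.3 SD. All of them concern levels, and the comparison of change removes part of the imbalance. The loss is therefore mainly one of precision and credibility. It is not systematic bias, although the ICC > 0.1 rule may take away the standard error that would otherwise allow for it.

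**What to change.** Have the independent co-worker randomise schools in permuted blocks within strata of school type. Alternatively, collect schools in registration batches and use constrained allocation on type, federal state and number of students. These factors are available at registration or from the consent letter that states the participating grades and classes. Baseline PSS-10 cannot be used, because under Participant timeline {13} it is collected 14–30 days after randomisation. Include the balancing factors as fixed effects in the primary model.

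The cost is a short script and a small delay for the first schools in a batch, with no extra students. Stratifying on both type and state may be too fine: two types by three states make six cells, or 24 / 6 = 4 schools per cell on average. School type should therefore come first.
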